### Sample size

Sample size was estimated according to previous study using the following formula [22]:
$$ n=\frac{{\left(\kern0.28em {Z}_{1-a/2}+{Z}_{1-\beta}\kern0.28em \right)}^2\kern0.28em \left(\kern0.28em {S}_1^2+{S}_2^2\kern0.28em \right)}{{\left({\mu}_1-{\mu}_2\right)}^2} $$

Based on a study by Jamilian et al. [22], the mean ± standard deviation [SD]) of FBS in co-supplementation of vitamin D and omega-3 and placebo groups were considered as 86.8 ± 6.40 and 94.6 ± 10.30, respectively. Given the type I and II error by 5% and 20%, respectively, the calculated sample size was 20 in each group. Since we want to perform five pairwise comparisons between the study groups, the sample size was increased to 38 individuals in each group for multiple adjustment. By considering four groups and an attrition rate of 10%, the estimated sample size was 168 individuals [24].

To achieve the target sample size, all invited patients who will come the Shahid Rastravesh Health Center will be included if they are willing to participate in the study (considering the inclusion criteria of the study).

Finally, a total number of 168 women will be allocated equally to four groups using the stratified permuted block randomization method.

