
### Statistical analysis

The effect of the intervention on all participants will be assessed based on intention-to-treat and per-protocol analyses. The data will be checked for plausibility by randomly checking the accuracy and completeness and source data verification. The normality of continuous variables will be determined using a Kolmogorov–Smirnov test. Appropriate statistical transformation (logarithmic transformation, square root transformation, cube root transformation, or reciprocal transformation) will be used for continuous variables with not normal distribution.

Hence, statistical analysis for continuous variables with normal distribution (parametric tests) will be used in this study.

Continuous variables with normal distribution and transformed variables will be expressed as mean ± SD. Categorical data will be presented as frequency (percentage).

To compare the mean differences within each group, before and after intervention, the paired t-test will be used for continuous variables.

For continuous variables, one-way analysis of variance (ANOVA) will be used to detect differences in sociodemographic characteristics, metabolic profiles, physical activity levels, and dietary intakes at the study baseline between the four groups.

Categorical data at the study baseline will be analyzed using the Chi-squared test between the intervention groups.

Repeated measures analysis of variance (RM ANOVA) with Bonferroni procedure to adjust for the five comparisons will be used to assess time effects and time-by-treatment (vitamin D and/or omega-3) interaction effects on all outcome variables between groups.

Since we have multiple endpoints and we will compare five pairwise comparison, all *p* values will be corrected using the Bonferroni adjustment method.

Two-way RM ANOVA with Bonferroni adjustment for comparisons will be used to assess the relationship between changes in mean serum vitamin D level and each of fasting blood sugar and other outcome variables between groups.

Levenes test for independent data in one-way ANOVA and Mauchly’s test in RM ANOVA will be used to test homoscedasticity.

All statistical measurements will be reported with 95% confidence intervals (CI). A *p* value < 0.05 will be considered statistically significant. All statistical analyses will be performed using SPSS version 24.

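### The Bonferroni family is stated two ways, so the threshold for the primary FBS contrasts is not fixed; only the five-comparison family matches the sample-size basis.

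*Protocol article*

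**What the plan says.** The Statistical analysis section of the protocol article describes the multiplicity correction in two consecutive paragraphs.

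- The repeated measures ANOVA is run on all outcome variables "with Bonferroni procedure to adjust for the five comparisons".
- The next paragraph corrects all p values by Bonferroni and gives two reasons: "Since we have multiple endpoints and we will compare five pairwise comparison". It states no divisor and does not set FBS apart.

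The same section reports all measurements with 95% confidence intervals and takes p below 0.05 as significant. It does not say whether the intervals carry the correction.

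Two other sections bear on which family is meant. Primary outcomes names one outcome, the eight-week difference in FBS between the four groups. Sample size raises the number per group for one reason: "Since we want to perform five pairwise comparisons between the study groups". It mentions no allowance for several endpoints.

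**The concern.** A Bonferroni rule is defined by its divisor, and the two paragraphs point to different ones. The first gives five. The second names multiple endpoints as a further reason for correction and covers every p value, which read literally means comparisons multiplied by endpoints.

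For a single primary outcome, error on the primary question is controlled by correcting over its own five contrasts. Adding secondary endpoints to that family is not needed for this and costs power. An FBS contrast with an unadjusted p between about 0.0006 and 0.01 would be positive under one paragraph and could be negative under the next. The text leaves that choice open until after the data are seen.

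**Working it through.** **Inputs from Sample size.** The group means and SDs "were considered as 86.8 ± 6.40 and 94.6 ± 10.30, respectively" give a difference of 94.6 − 86.8 = 7.8 and a root-mean-square SD of √((6.40² + 10.30²)/2) = 8.575. There are 38 evaluable women per group, and 168/4 = 42 randomised per group.

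**Reproducing the plan's figure.** The plan states: "Given the type I and II error by 5% and 20%, respectively, the calculated sample size was 20 in each group". Its formula gives (1.960 + 0.842)² × (6.40² + 10.30²)/7.8² = 18.97, so 19. A noncentral t calculation gives exactly 20. The total also follows: 38 × 4 × 1.10 = 167.2, so 168.

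The step from 20 to 38 does not reproduce at the stated 80% power. With alpha 0.05/5 = 0.01 the formula gives 28.2, so 29 (30 by t). By t, 38 corresponds to 90% power at alpha 0.01. The inflation is therefore more than enough for a divisor of five.

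**Counting endpoints (assumption; the article gives no total).** From Objectives and Assessments and measurements:

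- glucose indices and lipids: 8
- anthropometric indices: 3
- blood pressures: 2
- DASS-21: 1 total or 3 subscales
- PSQI: 1

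The sum is 15 to 17. Five contrasts each gives a divisor of 75 to 85, so alpha is 0.05/75 = 0.00067 to 0.05/85 = 0.00059.

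**Power for 7.8 on the planning SDs.** With 38 per group the standard error is 8.575 × √(2/38) = 1.967, and 7.8/1.967 = 3.965. Normal-approximation power is Φ(3.965 − z), where z is the two-sided critical value. With 42 per group, 3.965 becomes 4.169. The t columns use the two-group degrees of freedom, 2n − 2.

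| Divisor | alpha | z | 38 per group, t | 38, normal | 42 per group, t | 42, normal |
|---|---|---|---|---|---|---|
| 5 | 0.01 | 2.576 | 90.3% | 91.8% | 93.4% | 94.4% |
| 75 | 0.00067 | 3.403 | 65.8% | 71.3% | 73.2% | 77.8% |
| 85 | 0.00059 | 3.437 | 64.4% | 70.1% | 71.9% | 76.8% |

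Pooling the error variance over four groups (148 degrees of freedom) gives 91.1%, 68.6% and 67.3% at 38 per group, inside the same range. At divisors of 75 to 85, 80% power by t needs 47 to 48 evaluable per group.

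**Change scores.** The primary outcome is a change from baseline, and the article gives no correlation r between visits. If the SDs are equal at both visits (an assumption), the SD of a change is the planning SD × √(2(1 − r)). At 38 per group and a divisor of 85, power by t is 41% at r = 0.3, 64% at r = 0.5, 79% at r = 0.6 and 93% at r = 0.7.

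**Intervals.** With 38 per group, the half-width for a difference on the planning SDs is 3.9 for an ordinary 95% interval and 5.2 for a 99% interval, which is the level that matches a divisor of five.

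**The case against.** The strongest reply is that only one rule is meant. The first paragraph already covers all outcome variables, so it can be read as five comparisons within each endpoint, with the second paragraph merely giving the reason for doing this throughout. The later sentence on vitamin D changes again speaks of adjustment for comparisons, and the sample size rests on five comparisons alone. No section states a divisor of 75 or 85. This reading is possible, and it stands against anyone who would infer that the plan has committed itself to testing FBS at about 0.0006. It does not remove the defect: the second paragraph gives multiple endpoints as a reason for correction, and a divisor of five does nothing about endpoints.

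A reader might also infer that the trial is underpowered for its primary outcome. The documents do not support that. The loss depends on the wide reading, on an endpoint count that the article does not give, and, for change scores, on an unstated correlation. A literal reading of all p values would take in still more tests, such as the within-group paired t-tests, so 75 to 85 is itself a choice.

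Nor does the article show that its intervals contradict its tests. It never says that the 95% intervals are unadjusted. All that can be said is that ordinary 95% intervals would not match adjusted tests.

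Two further replies have some weight. A wider Bonferroni family is conservative and does not inflate type I error; its cost is power. And the Discussion part of the abstract describes the primary aim broadly, across glycemic, lipid, psychological, blood pressure and anthropometric measures, which lends the wide family some rationale. That makes it more important to say which family applies, because the outcomes section names FBS alone.

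**Conclusion.** The point holds as an ambiguity in a rule that decides the primary result. The Bonferroni family is described in two ways, and only the five-comparison family agrees with the sample-size basis and the single primary outcome.

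If the second paragraph is followed literally across endpoints, power for combination versus placebo falls by roughly 20 to 26 percentage points at 38 per group and misses the planned 80% whether 38 or 42 per group are analysed. This rests on the planning difference and SDs and on the assumed 15 to 17 endpoints. For the planned analysis of change, the direction and size of the departure from these figures cannot be settled from the article.

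**What to change.** State that the primary Bonferroni family is the five FBS contrasts only, each tested at alpha 0.01, and report 99% confidence intervals for these contrasts beside the adjusted tests.

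Replace the paragraph that corrects all p values on account of multiple endpoints with a separate rule for secondary endpoints that does not enter the FBS family. One option is Bonferroni over the five contrasts within each endpoint, with the results interpreted as supportive.

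The change is wording only and needs no more participants. The downside is that secondary findings carry no trial-wide confirmatory claim.

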## Methods/design

### Study design

This is an eight-week 2 × 2 factorial, triple-blinded (study investigators, participants, and statistical analyzer), randomized, placebo-controlled trial. Overall, 168 women of reproductive age diagnosed with prediabetes (fasting glucose 100–125 mg/mL) will be screened for enrolment in the study. This study will be conducted at Shahid Rastravesh Health Center Laboratory, Alborz University of Medical Sciences, Karaj, Iran.

Eligible participants who meet the inclusion and exclusion criteria will be randomly divided into four groups to receive double placebo (omega-3 and vitamin D placebos), omega-3 placebo and vitamin D supplement, omega-3 supplement and vitamin D placebo, and supplements of omega-3 and vitamin D.

In this factorial 2 × 2 design, we want to address five questions:
Compared to placebo, is omega-3 effective?Compared to placebo, is vitamin D effective?Are vitamin D + omega-3 more effective than placebo?Are vitamin D + omega-3 more effective than vitamin D alone?Are vitamin D + omega-3 more effective than omega-3 alone [24]?

Participants will visit the trial sites three times: at baseline (0 weeks); after three days; and post intervention (eight weeks after intervention). The flow chart of the study protocol is presented in Fig. 1.

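### Single-step Bonferroni for the five comparisons is valid but needlessly conservative: Holm's step-down version gives the same 5% guarantee and never rejects less

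*Protocol article*

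**What the plan says.** The Study design section lists five questions: each supplement against placebo, the combination against placebo, and the combination against each supplement alone. One of them reads "Are vitamin D + omega-3 more effective than vitamin D alone". The Sample size section treats these as one set ("Since we want to perform five pairwise comparisons between the study groups") and raises the number per group to 38 because of them.

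The Statistical analysis section then names the adjustment twice. Repeated measures ANOVA "with Bonferroni procedure to adjust for the five comparisons will be used to assess time effects" and time-by-treatment interactions. A later sentence, which cites multiple endpoints as well as the five comparisons, says all p "values will be corrected using the Bonferroni adjustment method". No step-down, closed or hierarchical procedure is mentioned, and no reason is given for the single-step form. The section promises 95% confidence intervals and does not say whether they are adjusted for multiplicity.

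**The concern.** Single-step Bonferroni tests every comparison in a family of five at 0.01, even after some of the five hypotheses have been rejected. Holm starts at the same 0.01 but relaxes the threshold after each rejection. It needs no further assumption about the correlation between the comparisons, which share arms here. For testing, the protocol has therefore fixed a procedure that another equally simple one dominates.

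What is at stake is power, not the error rate. The trial was sized on the combination against placebo only. The other four comparisons include the two that ask whether co-supplementation adds anything to either supplement alone. No effect was planned for them, and they are where a gain could change a conclusion.

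**Working it through.** **Inputs from the Sample size section.** FBS means and SDs for combination and placebo "were considered as 86.8 ± 6.40 and 94.6 ± 10.30, respectively": difference 94.6 − 86.8 = 7.8, and root-mean-square SD = √((6.40² + 10.30²)/2) = 8.57. Error rates: "Given the type I and II error by 5% and 20%, respectively, the calculated sample size was 20 in each group", two-sided by the printed formula. After adjustment, 38 per group.

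**The plan's own figures.** n = (z₁₋α/₂ + z₁₋β)²(S₁² + S₂²)/(μ₁ − μ₂)².
- α = 0.05, 80% power: 18.97, so 19 (stated 20; close).
- α = 0.05/5 = 0.01, 80% power: 28.23, so 29 (stated 38; not reproduced).
- 38 × 1.10 = 41.8, so 42 per group and 4 × 42 = 168 (stated total reproduced).

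The gap between 29 and 38 is a separate matter. Here it only means that the planned comparison has spare power.

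**The two rules on the same five p values.**
- Bonferroni: reject any p ≤ 0.01.
- Holm: order the p values and compare them in turn with 0.05/5 = 0.01, 0.05/4 = 0.0125, 0.05/3 = 0.0167, 0.05/2 = 0.025 and 0.05, stopping at the first failure.

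No Holm threshold is below 0.01, so every Bonferroni rejection is also a Holm rejection.

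**Power at 0.01 by formula.** Standard error = 8.57 × √(2/38) = 1.967.
- Difference 7.8: 7.8/1.967 = 3.965, and Φ(3.965 − 2.576) = 91.8% (about 91% with a pooled t on 148 df).
- Difference 3.9: 3.9/1.967 = 1.983, and Φ(1.983 − 2.576) = 27.6% (about 27% with the t).

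**Simulation.** At least 200,000 four-arm trials per scenario, 38 per arm, common SD 8.57, pooled t on 148 df, the protocol's five comparisons. The effect of each single supplement is an assumption, because the protocol states none.

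| Assumed effect of each supplement alone | Comparison | Bonferroni | Holm |
|---|---|---|---|
| 1.95 (quarter) | single vs placebo | 6% | 9% |
| | combination vs single | 64% | 70% |
| | combination beats both singles | 49% | 58% |
| | combination vs placebo | 91% | 92% |
| 3.9 (half, additive) | each of the four half-size comparisons | 27% | 34% |
| | combination beats both singles | about 13% | about 21% |
| | combination vs placebo | 91% | 91% |
| 5.85 (three-quarter) | single vs placebo | 64% | 70% |
| | combination vs single | 6% | 9% |
| | combination vs placebo | 91% | 92% |
| 0 (combination only) | each combination comparison | 91% | 93% |
| | all three combination comparisons | 80% | 86% |

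The 6% to 9% rows are a gain of about 4 points before rounding (5.7% to 9.6% by the normal approximation). With single effects of 1.95 to 5.85, Holm added at least one rejection in about 17% to 22% of trials. It never lost a Bonferroni rejection.

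**Family-wise error.** Under the global null it was 4.3% for both rules. Under the partial nulls it was about 2% for Bonferroni and 4.1% to 4.2% for Holm. Both are within 5%.

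**The case against.** The strongest reply is that nothing here is wrong. Bonferroni is pre-specified, valid under any dependence and consistent with the sample-size section, so preferring Holm is close to a matter of taste. That stands as far as validity goes. A reader might infer that the protocol's error control is faulty, and the documents do not support that. What remains is that a better test is available at almost no cost.

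The gains also rest on effects the protocol does not state, and on SDs of FBS itself, whereas the primary outcome is change from baseline analysed by repeated measures ANOVA. This stands too: the absolute percentages may not carry over. The ordering of the two rules does not depend on them.

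Three further inferences fail. First, Holm does not help most where power is lowest: at quarter or three-quarter effect the weakest comparisons gain about 4 points and those near 64% gain about 6. Second, Holm does not rescue the combination questions, since 34% or 21% is still poor power. Third, the protocol poses five separate questions and nowhere requires joint success. If beating both single supplements were the only claim, requiring both tests to succeed would protect it at 5% without adjustment.

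Bonferroni also has simple matching simultaneous intervals, which is a fair reason to keep it. The protocol does not give that reason and describes no adjusted intervals.

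Finally, the sentence naming multiple endpoints leaves the family open. The figures above assume a family of five. Holm is at least as powerful for whatever family is settled, and the unclear family is a separate point.

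**Conclusion.** The point holds as an avoidable loss of efficiency, not as an error. Under a five-comparison family with 38 completers per arm, SD 8.57 and a combination-placebo difference of 7.8, Holm adds about 4 to 7 points to the comparisons other than combination versus placebo when each single supplement has an effect of 1.95 to 5.85. The chance that the combination beats both single supplements rises by about 8 to 9 points at half and quarter effect. The planned comparison gains 2 points at most. The weak comparisons remain underpowered under either rule. That Holm dominates Bonferroni for testing needs none of these assumptions; the size of the gain needs all of them.

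**What to change.** In the Statistical analysis section, name Holm's step-down Bonferroni procedure for the five FBS comparisons, report Holm-adjusted p values, and base significance on them. Make the change before unblinding.

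Also say how the intervals relate to the tests. The plan promises 95% intervals; if simultaneous ones are wanted, single-step 99% intervals would be an addition, since the plan has none now. Either way, state that the intervals need not match the Holm decision.

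The cost is wording and a little arithmetic on unadjusted p values, with no extra participants. The real downside is that a comparison significant by Holm with a raw p between 0.01 and 0.05 can have a 99% simultaneous interval that includes zero. If the investigators value exact agreement between test and interval more than the extra power, keeping Bonferroni is defensible, but the protocol should then say so.

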### Objectives

Compare the mean serum lipid (triglycerides [TG], total cholesterol [TC], low-density lipoprotein cholesterol [LDL-C], high-density lipoprotein cholesterol [HDL-C]) and glucose indices (fasting blood sugar [FBS], fasting blood insulin [FBI], homeostasis model assessment - insulin resistance [HOMA-IR], homeostasis model assessment - beta cell function [HOMA-B]) between the four groups and within each group, before and after intervention.Compare the means of anthropometric indices (weight, waist circumference, body mass index [BMI]) and systolic and diastolic blood pressures between the four groups and within each group, before and after the intervention.Compare the mean scores of the Depression Anxiety Stress Scale (DASS-21) and Pittsburgh Sleep Quality Index (PSQI) between the four groups and within each group, before and after intervention.Determine the relationship between changes in mean level of serum vitamin D and each of the glucose indices, serum lipids, and the mean scores of the DASS-21 and PSQI between the four groups and within each group, during intervention.

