### Assessments and measurements

Participants will be visited at the Shahid Rastravesh Health Center three times, at baseline, after three days and after eight weeks. Participants will be interviewed regarding their sociodemographic background at baseline.

Then, at the beginning and eight weeks after the intervention, the following will be done:
Blood sample will be drawn after at least 12 h of fasting. All blood samples will be centrifuged at 3000 rpm for 10 min and serum will be separated into clean tube aliquots and stored at – 80 °C until analysis [12]. Collection of blood, specimen storage, and laboratory tests will be conducted at the Shahid Rastravesh Health Center laboratory in Karaj. To determine FBS, serum triglycerides, TC, and HDL-C concentrations, we will use an enzymatic kit (Pars Azmun, Tehran, Iran). LDL-C will be estimated based on the Friedewald equation [27]. Serum level of vitamin D and insulin will be quantified using a commercial enzyme-linked immunosorbent assay kit (Monobind, CA, USA).The HOMA-IR and HOMA-B will be determined according to suggested formulas [29].

$$ \mathrm{HOMA}-\mathrm{IR}=\left[\mathrm{FBI}\ \left(\upmu \mathrm{U}/\mathrm{mL}\right)\mathrm{x}\ \mathrm{FBS}\ \left(\mathrm{mg}/\mathrm{ml}\right)\right]/405 $$
$$ \mathrm{HOMA}-\mathrm{B}=\left[\mathrm{FBI}\ \left(\upmu \mathrm{U}/\mathrm{mL}\right)\ \mathrm{x}\ 360/\mathrm{FBS}\ \left(\mathrm{mg}/\mathrm{ml}\right)-63\right]\% $$

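### The two-way repeated measures ANOVA named for the fourth objective compares means and gives no estimate of how change in serum vitamin D relates to change in the outcomes

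*Protocol article*

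**What the plan says.** The last of the four items under Objectives reads: "Determine the relationship between changes in mean level of serum vitamin D and each of the glucose indices, serum lipids". It goes on to the DASS-21 and PSQI scores and asks for this both between the four groups and within each of them.

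Statistical analysis gives that objective one sentence: "Two-way RM ANOVA with Bonferroni adjustment for comparisons will be used to assess the relationship between changes in mean serum vitamin D level". On the other side of the relationship it puts FBS and the remaining outcomes, compared across arms. It does not name the two factors, and it mentions no covariate.

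Earlier in the same section, repeated measures ANOVA is described as a method "to assess time effects and time-by-treatment (vitamin D and/or omega-3) interaction effects on all outcome variables between groups". That is a comparison of means over time and treatment.

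Vitamin D itself is a measured concentration. According to Assessments and measurements, "Serum level of vitamin D and insulin will be quantified using a commercial enzyme-linked immunosorbent assay kit", and blood is drawn "at the beginning and eight weeks after the intervention, the following will be done". Each woman therefore has one continuous change in vitamin D and one change in each outcome. Neither the Abstract's list of methods nor Statistical analysis names a correlation, a regression, an ANCOVA or any model with vitamin D change as a predictor.

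**The concern.** A relationship between two changes is described by a slope or a correlation, and both depend on how the two changes vary together across women. Repeated measures ANOVA by arm and time handles one response variable at a time and asks whether its mean moves differently across categories. Bonferroni-adjusted contrasts of arm means do not supply the missing quantity.

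The within-group half of the objective shows this most plainly. Inside a single arm only the time factor is left, and the paired t-test already planned covers it.

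At stake is one declared objective. Followed as written, its analysis repeats the preceding repeated measures ANOVA and leaves the question without an estimate.

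**Working it through.** **Inputs.** Sample size gives the FBS assumptions (they "were considered as 86.8 ± 6.40 and 94.6 ± 10.30, respectively"), 38 women per group after the multiplicity adjustment, four groups, 10% attrition and a total of 168. Statistical analysis gives five pairwise comparisons with Bonferroni correction. There are two measurement times, baseline and week 8.

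**The plan's own figures.** The point rests on no stated number, but the analysed total is needed below.
- Base size: (1.960 + 0.842)² × (6.40² + 10.30²) / 7.8² = 18.97, so 19 per group, or 20 with the t distribution. The article states 20.
- Completers: 38 × 4 = 152. Inflated: 152 × 1.10 = 167.2, or 42 per arm = 168, as stated.

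**Does the named method respond to the association?** With two time points, the time-by-arm F equals the one-way ANOVA F on change scores. I took four arms of 38. The means and SDs are my assumptions for illustration, not figures from the article:
- Vitamin D change: means 0, 0, 12, 12; SD 5.
- FBS change: means 0, -2, -3, -5; SD 8.

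For FBS the grand mean is -2.5 and the squared deviations sum to 6.25 + 0.25 + 0.25 + 6.25 = 13. So F = (38 × 13 / 3) / 8² = 164.67 / 64 = 2.573 (p = 0.056).

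For vitamin D the grand mean is 6 and the squared deviations sum to 4 × 36 = 144. So F = (38 × 144 / 3) / 5² = 1824 / 25 = 72.96.

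The correlation between the two changes enters neither expression. The arm-adjusted slope of FBS change on vitamin D change is r × 8/5:

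| Within-arm r | F, FBS | F, vitamin D | Slope (FBS units per ng/mL) |
|---|---|---|---|
| -0.8 | 2.573 | 72.96 | -1.28 |
| 0 | 2.573 | 72.96 | 0 |
| +0.8 | 2.573 | 72.96 | +1.28 |

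Other assumed means and SDs would change the F values, but they would still be the same in all three rows.

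**Why arm must be in the model.** In the middle row the correlation pooled over arms is -0.143, although every arm has zero association. The pooled figure comes entirely from the differences between arm means.

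**What a suitable model could detect at 80% power.** For a partial correlation with k covariates, detectable r = tanh[(z for alpha + 0.842) / √(N − 3 − k)]. With baseline outcome, baseline vitamin D and three arm terms, k = 5:
- N = 152, alpha 0.05: tanh(2.802 / √144) = 0.229, about 0.23.
- N = 152, alpha 0.05/5 = 0.01: tanh(3.418 / √144) = 0.277, about 0.28.
- One arm of 38, alpha 0.05, no covariates: tanh(2.802 / √35) = 0.44.

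For a correlation near zero, the 95% half-width is tanh(1.96 / √35) = 0.32 in one arm and tanh(1.96 / √149) = 0.16 over 152 women.

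**The case against.** **The wording may be meant at group level.** Both sentences speak of changes in mean vitamin D, and the analysis sentence refers to differences between groups. On that reading the aim is to see whether arms whose mean vitamin D rises also show movement in FBS. This is a fair reading of loose wording, and the objective may be as much at fault as the method. It does not rescue the sentence. It repeats the repeated measures ANOVA already planned for all outcomes, it cannot serve the within-group part, and lining up four arm means does not estimate a relationship.

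**A repeated measures model can take a continuous covariate.** With vitamin D change entered, the time-by-covariate term is a slope of change on change. This is correct, and it means that the fault lies in the specification and not in the software. But the article mentions no covariate, and its adjustment for comparisons points to contrasts between arms.

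**The article is condensed, and a fuller protocol or SAP may do better.** That would excuse silence. Here a method is stated, and it does not fit its objective.

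**The objective is minor.** This stands. It is outside the primary outcome, the listed secondary outcomes, the five design questions and the sample size basis. The article does not label it exploratory; I use the word because of where it stands.

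**Misreporting.** A reader might infer that the trial will present a treatment effect as a dose-response with vitamin D. Nothing in the article announces such an interpretation, so I do not rely on it.

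**Conclusion.** The point holds at moderate severity. The only method stated for the fourth objective yields no slope or correlation, so that objective gets no estimate. The conclusion assumes that the two factors are categorical: arm and time, or the two supplement assignments with time.

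Two stronger readings are not supported. The first is that the main analysis is undermined: the primary FBS comparison and the sample size do not depend on this sentence, and no randomised comparison is biased by it. The second is that the objective is beyond the trial's data: both serum measurements are planned, and a regression would use them.

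The data also have limits. Across about 152 completers, detectable partial correlations are about 0.23 (alpha 0.05) or 0.28 (alpha 0.01, five comparisons). The plan's wider correction for multiple endpoints would raise these further. Within a single arm of 38 the figure is about 0.44 even at alpha 0.05, so only strong within-group associations could be shown.

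**What to change.** Replace the sentence on two-way repeated measures ANOVA with wording such as: *For each outcome, the week-8 value will be regressed on the change in serum vitamin D, adjusted for the baseline value of the outcome, baseline vitamin D (or randomisation stratum) and treatment arm. An arm-by-change term will give the slope within each group. Slopes will be reported with 95% confidence intervals.*

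Add three statements:
- The slopes are exploratory and observational, because vitamin D change arises after randomisation.
- Adjustment for arm means that the slope describes the association within arms and leaves out the contrast between supplemented and unsupplemented arms.
- Within-group slopes will be imprecise at about 38 women per arm. The plan should also say whether the Bonferroni rule applies to them.

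Regression of change on change, or a repeated measures model with vitamin D change entered explicitly as a covariate, would also serve if written out. The cost is one sentence and a short qualification, recorded before unblinding. No new data, visits or participants are needed.
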